### **2.3.2 Exclusion Criteria:**

1. Postoperative pathology indicating parametrial involvement.
2. Patients who received chemotherapy before radiotherapy.
3. Bilateral hydronephrosis, inability to place ureteral stents, or inability to perform nephrostomy.
4. Distant metastasis.
5. History of ulcerative colitis or Crohn's disease.
6. Other active malignancies.
7. Pregnant or breastfeeding patients.
8. Contraindications to cisplatin chemotherapy.
9. Severe underlying medical conditions that preclude safe administration of study treatment, including but not limited to persistent or active infection, symptomatic congestive heart failure, unstable angina, arrhythmias, or psychiatric/social conditions that may limit adherence to study requirements.
10. HIV positive.

### **2.3.3 Withdrawal Criteria:**

Participation in this study is voluntary, and patients may withdraw at any time. Patients may be withdrawn or excluded from study treatment for the following reasons:

1. Inability to continue follow-up.
2. Patient withdrawal of consent.
3. Changes in the patient's condition that the investigator deems necessitate stopping treatment.

## **2.4 Trial Process**

[figure not shown]

## 2.5 Main Research Content:

### 2.5.1 Radiotherapy

Radiotherapy must begin within 4 weeks after randomization.

#### 2.5.1.1 External Beam Radiotherapy Equipment:

Linear accelerator, 6MV-X-rays.

#### 2.5.1.2 External Beam Radiotherapy Technique:

- Patients are required to drink 500 ml of water one hour before simulation to ensure bladder fullness.
- CT simulation is performed with the upper boundary at the inferior edge of

278 T10 and the lower boundary at the vulvar opening, with 5 mm slice thickness.

279 • Radiotherapy is delivered using intensity-modulated radiation therapy (IMRT)  
280 techniques.

281 • The pelvic field CTV includes internal iliac, external iliac, common iliac,  
282 obturator, presacral, uterine cervix, corpus uteri, adnexal areas, parametrial  
283 tissue, part or all of the vagina, and the extended field CTV includes the pelvic  
284 field plus the para-aortic lymph node drainage area, with the upper boundary  
285 at the level of the left renal vein.

286 • Specific target delineation refers to the "Fudan University Shanghai Cancer  
287 Center Gynecological Oncology Target Delineation Guidelines."

288 • The PTV is expanded 0.8 cm from the CTV.

289 • Patients are required to drink 500 ml of water one hour before radiotherapy to  
290 maintain bladder fullness.

291 The upper boundary of the external beam plan is generally at the level of the  
292 aortic bifurcation, and the lower boundary is determined based on the extent of  
293 vaginal involvement. The target area must include the tumor bed, parametrium,  
294 uterosacral ligaments, presacral lymph nodes, and other potentially involved lymph  
295 nodes, as well as sufficient vaginal tissue. If common iliac or para-aortic lymph node  
296 metastasis has occurred, extended field irradiation is required, with the upper  
297 boundary reaching the level of the renal vessels or extended cephalad based on the  
298 lymph node involvement.

### 299 **2.5.1.3 External Beam Dose:**

300 Conventional fractionation is used, with 1.8 Gy per fraction, 5 fractions per week.  
301 Total dose: 50.4 Gy over 5 weeks. The dose uniformity within the target area should  
302 be within  $\pm 5\%$ , while evaluating organs at risk, such as the rectum, sigmoid colon,  
303 bladder, small intestine, ilium, sacrococcygeal bone, pubis, femoral head, and femoral  
304 neck.

---

|            |                                       |
|------------|---------------------------------------|
| PTV | V50.4 $\geq 95\%$ , Dmax $\leq 107\%$ |
|------------|---------------------------------------|

|                  |                                         |
|------------------|-----------------------------------------|
| PTV-boost | V58.8 $\geq 95\%$ , Dmax $\leq 107\%$ , |
|------------------|-----------------------------------------|

---

|                        |                                |
|------------------------|--------------------------------|
| Rectum          | V60<=30%; D2cc<=105%           |
| Bladder         | V60<=30%; D2cc <=105%          |
| Small Intestine | V30<=40%; V40<=30%; D2cc<=105% |
| Femoral Head    | V30<20%                        |
| Kidneys         | V15<50%                        |
| Spinal Cord     | Dmax<45Gy                      |

#### **2.5.1.4 Simultaneous Integrated Boost:**

During the external beam target delineation process, the tumor bed area will be given a simultaneous integrated boost of 58.80 Gy/2 8 fractions. The upper boundary is 2 cm above the femoral head, the lower boundary is 2cm inferior to the vaginal cuff, the two laterally sides are the medial edge of the internal obturator muscle and the pubococcygeus muscle, the front boundary includes the posterior wall of the bladder, and the posteriorly boundary is the part where the residual sacral ligament and the rectal mesentery fuse with the sacral ligament.

#### **2.5.2 Chemotherapy:**

Concurrent chemotherapy with cisplatin will be administered during radiotherapy. The specific dose is 40 mg/m^2, administered based on patient weight on the day of radiotherapy. Chemotherapy will not be given on days without radiotherapy, and a maximum of five doses will be administered. Chemotherapy should be scheduled from Monday to Wednesday, avoiding Thursday and Friday. All toxicities will be graded according to the National Cancer Institute (NCI) Common Terminology Criteria for Adverse Events (CTCAE) version 4.0. No chemotherapy will be administered until all drug-related toxicities (except anemia) of  $\geq$  Grade 2 have resolved to Grade 1. It is recommended to correct anemia (Hb < 10 g/dL) with blood transfusion as soon as possible. No dose escalation will be performed in this study. No chemotherapy will be administered during radiotherapy delays. Radiotherapy will not be delayed due to chemotherapy-related toxicities unless the investigator deems the patient too weak to undergo treatment. Only one dose reduction is allowed for

328 cisplatin administration.

329

| Drug      | Starting Dose Level | Dose Level -1       |
|-----------|---------------------|---------------------|
| Cisplatin | 40mg/m  | 30mg/m  |

330 **Drug-Related Toxicity Adjustments:**

| Toxicity                           | Parameter                                                                                                  | Adjustment                                                                                                                                                                  |
|------------------------------------|------------------------------------------------------------------------------------------------------------|-----------------------------------------------------------------------------------------------------------------------------------------------------------------------------|
| Febrile
Neutropenia/ANC | First occurrence of febrile neutropenia
( $\geq$ Grade 3) or ANC $< 0.5 \times 10^9/L$
for $>7$ days | Hold for 1 week. Repeat blood tests. If
ANC resolves to Grade 1, resume at
reduced dose level. If ANC does not
resolve, discontinue cisplatin.                     |
| Febrile
Neutropenia/ANC | Second occurrence                                                                                          | Discontinue cisplatin.                                                                                                                                                      |
| ANC                                | Non-complex (no fever/infection)
ANC $< 0.5 \times 10^9/L$ for $<7$ days                                | No dose reduction, but do not retreat until
ANC resolves to Grade 1.                                                                                                     |
| Platelets                   | First occurrence of Grade 4
thrombocytopenia or bleeding with
Grade 3 thrombocytopenia               | Hold for 1 week. Repeat blood tests. If
platelets $>75 \times 10^9/L$ , resume at reduced
dose level. If thrombocytopenia does not
resolve, discontinue cisplatin. |
| Platelets                   | Second occurrence                                                                                          | Discontinue cisplatin.                                                                                                                                                      |
| Platelets                   | Grade 3 – non-complex (no bleeding)                                                                        | Hold treatment until platelets $>75 \times 10^9/L$ ,
then resume at current dose level (no
adjustment).                                                               |
| Nausea/Vomiting             | Grade 3 or 4                                                                                               | Hold treatment until resolution to Grade 1
(with supportive care). Resume at reduced
dose level.                                                                      |
| Nausea/Vomiting             | Second occurrence                                                                                          | Discontinue cisplatin                                                                                                                                                       |

|                                                        |                                                                                                    |                                                                                                                                                                               |
|--------------------------------------------------------|----------------------------------------------------------------------------------------------------|-------------------------------------------------------------------------------------------------------------------------------------------------------------------------------|
| Serum Creatinine/GFR                            | GFR < 50 ml/min (Cockcroft-Gault) or
GFR < 40 ml/min (measured creatinine
or EDTA clearance) | Hold for 1 week. Repeat blood tests. If
GFR recovers to the above level at the
same dose, resume treatment. If not
recovered after 1 week, discontinue
cisplatin. |
| Neurotoxicity –
Peripheral Neuropathy | ≥ Grade 2                                                                                          | Hold treatment until neuropathy resolves
to Grade 1. Resume at reduced dose level.

If neuropathy does not resolve within 21
days, discontinue cisplatin.         |
| Tinnitus or Hearing Loss                        | Grade 3 or 4                                                                                       | Discontinue cisplatin.                                                                                                                                                        |
| Tinnitus or Hearing Loss                        | Grade 2                                                                                            | Hold treatment until resolution to Grade
1, then resume at reduced dose level.

Audiometry should be performed to
determine if hearing loss is reversible.        |
| Fatigue                                         | Any grade                                                                                          | No dose reduction required.                                                                                                                                                   |
| Other Non-Hematologic
Toxicities            | ≥ Grade 3                                                                                          | Hold treatment until toxicity resolves to
Grade 1, then resume at the same dose. If
toxicity does not resolve to Grade 1
within 21 days, discontinue cisplatin.      |

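### Section 2.5.2 gives two different grades at which cisplatin is held for non-hematologic toxicity, and does not say which governs

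*Protocol*

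**What the plan says.** All the relevant wording is in Protocol Section 2.5.2.

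- **Text, general rule:** "No chemotherapy will be administered until all drug-related toxicities (except anemia") have settled. The threshold follows in the same sentence: toxicity at or above "Grade 2 have resolved to Grade 1". Anemia is the only exception named.
- **Table, catch-all row for other non-hematologic toxicities:** the trigger is Grade 3 or higher. The action is "Hold treatment until toxicity resolves to" Grade 1, then resumption at an unchanged dose. Cisplatin stops if there is no resolution within 21 days.
- **Table, nausea/vomiting:** the trigger is Grade 3 or 4. The action is "Hold treatment until resolution to Grade 1", then the reduced level. A second occurrence ends cisplatin.
- **Table, peripheral neuropathy:** the trigger is Grade 2 or higher, with "Hold treatment until neuropathy resolves" to Grade 1.
- **Table, tinnitus or hearing loss:** at Grade 2, "Hold treatment until resolution to Grade" 1, then the reduced level. At Grade 3 or 4 cisplatin stops.
- **Table, fatigue:** "No dose reduction required" at any grade. The row does not mention a hold.
- **Reductions:** "Only one dose reduction is allowed for" cisplatin, and only one lower level is defined (30 mg/m2, from 40 mg/m2).

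The same section limits cisplatin to radiotherapy days and to five doses. Radiotherapy does not wait for chemotherapy toxicity unless the investigator judges the patient too weak.

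**The concern.** Whether a patient receives this week's cisplatin is a safety decision, and a reader of the section should reach one answer. For Grade 2 nausea, or Grade 2 toxicity in the catch-all row, the text says to hold and the table triggers nothing. Two investigators could treat the same patient differently, and each could point to the protocol.

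Cisplatin is the shared backbone of both groups (Section 2.2.1). If its delivery depends on which rule is read, the background treatment on which the boost is tested is not well defined. Differences in exposure also become hard to interpret, because a dose withheld under one reading would have been given under the other.

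**Working it through.** The plan states no figure to reproduce. The check is a comparison of text and table, followed by simple arithmetic on what a hold can cost.

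**Step 1. What each source says at Grade 2**

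| Toxicity | Text | Table | Agreement |
|---|---|---|---|
| Other non-hematologic | Hold | No hold (starts at Grade 3) | No |
| Nausea/vomiting | Hold | No hold (Grade 3 or 4) | No |
| Peripheral neuropathy | Hold | Hold | Yes |
| Tinnitus or hearing loss | Hold | Hold | Yes |
| Fatigue | Hold, if drug-related | Addresses dose reduction only | Unclear |
| Creatinine/GFR | Hold, if graded 2 or higher | Uses GFR cut-offs, not grades | Not comparable by grade |

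**Step 2. Could the table be about dose changes only, with the text governing holds?** That works fairly well for nausea/vomiting, where Grade 3 or 4 also brings a dose reduction. It does not work for the catch-all row, which prescribes a hold and then the same dose. With no reduction attached, its Grade 3 trigger is a hold threshold, and it differs from the text. Because the table sets Grade 2 triggers for neuropathy and hearing loss, a reader may also take Grade 3 elsewhere as deliberate.

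**Step 3. If the text governs, is the rule complete?** Not quite. The 21-day limit in the catch-all row attaches to Grade 3 or higher. A lasting Grade 2 toxicity in that category would be held with no stated point for stopping.

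**Step 4. What a one-week hold can cost**

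- Planned cisplatin (Sections 2.2.1 and 2.5.2): 5 × 40 = 200 mg/m2. One lost dose is 40/200 = 20%.
- Radiotherapy (Section 2.5.1.3): 50.4/1.8 = 28 fractions. At five per week this is 28/5 = 5.6 weeks, although the section describes the course as 5 weeks.
- With a Monday start and no interruption, five weeks deliver 25 fractions and 28 − 25 = 3 fall on Monday to Wednesday of week six, which are permitted chemotherapy days.
- If a held dose may be given in week six, a one-week hold costs 0 doses. If cisplatin is confined to five calendar weeks, as Section 2.2.1 can be read, it costs 1.

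The range per one-week hold is therefore 0 or 1 of 5 doses, or 0 to 40 of 200 mg/m2. The documents give no Grade 2 toxicity rate, so the effect on mean exposure in the trial cannot be computed.

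**Step 5. After the single reduction.** Five toxicities lead to the reduced level at their first qualifying event: febrile neutropenia/ANC, platelets, nausea/vomiting, neuropathy and hearing loss. The rows for a second occurrence belong to individual toxicities, and neuropathy and hearing loss have none. A patient already at 30 mg/m2 who then has a different first toxicity could be read as staying at that level or as having used the only reduction allowed.

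**The case against.** The strongest reply is that both rules can be obeyed at once by following the stricter text. The table is headed as a list of adjustments. No row expressly permits dosing at Grade 2 nausea or other Grade 2 non-hematologic toxicity, and silence in a table does not cancel an explicit sentence. This stands as a possible reading, but the protocol does not adopt it, and the catch-all row, which holds without changing the dose, points the other way.

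Three stronger conclusions are tempting and are not supported.

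- **That the Grade 3 rows would be pointless if the text governs.** They would not. The nausea/vomiting row adds a reduction and a stopping rule, and the catch-all row adds same-dose resumption and the 21-day limit.
- **That the reduction rule contradicts the table.** Only one lower level exists, so a row calling for the reduced level can mean remaining there. This is an ambiguity.
- **That the mismatch biases the comparison against or for the boost.** The rules are identical in both groups. For exposure to diverge, boost-related bowel toxicity would have to be judged drug-related, or the rule applied differently by group, and the documents show neither. If the boost did lead to more withheld cisplatin, that would follow from assigned treatment and would belong to the intention-to-treat comparison in Section 2.5.7.3.

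**Conclusion.** The inconsistency is real and narrow. It is sharpest between the general rule in the text and the catch-all row, and less sharp for nausea/vomiting. The fatigue row and the step after a reduction are unclear but not contradictory. The size is 0 or 1 of five doses per one-week hold (at most 20% of planned cisplatin), assuming radiotherapy proceeds without delay and depending on whether week six may be used. Longer holds could cost more. No figure for mean exposure or for a difference between groups can be derived from the document. The point deserves correction because it concerns a safety rule for treatment that every patient receives.

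**What to change.** The sponsor's clinical team should reconcile the text of Section 2.5.2 with the nausea/vomiting and catch-all rows so that text and table give one hold threshold per toxicity. The same edit should say whether the fatigue row exempts fatigue from holds, and what applies to a patient already at the reduced level who has a different first toxicity. Which threshold or dose is right is a clinical decision and is not judged here.

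The report should show cisplatin doses received, held and reduced, by arm. If treatment is already complete, which is possible given the 2019–2020 surgery dates in Section 2.2.2, rewording cannot change exposure. This table, with a statement of which rule was followed in practice, then becomes the useful step.

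The cost is a short amendment and one descriptive table. The protocol does not list cisplatin doses among the case report form items, so it should be confirmed that doses and reasons for holding are recorded.

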### 2.5.3 Other Medications:

Anti-emetic therapy: Aprepitant 125 mg, dexamethasone 8 mg, ondansetron 8 mg;  
or a standard combination of a corticosteroid and a 5HT antagonist.

### 2.5.4 Efficacy Evaluation:

All patients will undergo routine baseline assessments, including clinical review,  
routine blood tests, and imaging studies (CT, MRI, or PET scans). Weekly follow-ups  
will be conducted during chemoradiotherapy, and clinical examinations will be  
performed every 3 weeks during adjuvant chemotherapy. Patients will then be

observed every 3 months for 2 years, followed by every 6 months for 5 years. It is planned that all patients will complete the treatment study, except in cases of disease progression or toxicity preventing further treatment. Regardless of treatment completion, quarterly follow-ups will be conducted for 2 years, then every 6 months for 3 years or until death. After completing all study treatments, treatment efficacy will be determined 6 months after randomization based on clinical examination and chest/abdominal/pelvic CT results. If suspicious lesions are present, PET scans should be repeated 4 to 6 months after completion of chemoradiotherapy, with priority given to PET-CT scans. CT scans should also be performed upon any recurrence to determine the observed pattern of recurrence. Progression-free survival (PFS) is defined as the time from randomization to investigator-determined disease progression or death from any cause. Overall survival is defined as the time from randomization to death from any cause.

#### **2.5.5 Safety Evaluation:**

Adverse events (AEs) are defined as any unfavorable medical event occurring in a patient or clinical study subject during the course of radiotherapy and chemotherapy. AEs do not necessarily have a causal relationship with the treatment. AEs include any unfavorable or unintended sign (including abnormal laboratory findings), symptom, or disease temporally associated with the study drug administration, regardless of whether it is considered treatment-related.

AEs include the following:

- All suspected drug or device reactions.
- All reactions from drugs or devices, including overdoses, drug abuse, drug sensitivity, toxicity, or failure of expected pharmacological effects (if applicable).
- Apparently unrelated illnesses, including exacerbations of pre-existing conditions (severity, frequency).
- Injuries or accidents.
- Abnormalities in physiological tests or physical examinations requiring

clinical intervention or further investigation (beyond predefined repeat tests).

- Laboratory abnormalities requiring clinical intervention or further investigation (beyond predefined laboratory tests).
- Any unfavorable event occurring during the reporting period specified in the protocol that the investigator considers related to the drug or device.

Even if they do not meet the criteria for serious adverse events (SAEs), AEs must be reported as AEs. SAEs are defined as any unfavorable medical event occurring at any dose that:

- Results in death.
- Is life-threatening (the subject is at immediate risk of dying at the time of the event).
- Requires inpatient hospitalization or prolongation of existing hospitalization.
- Results in persistent or significant disability or incapacity.
- Results in congenital anomaly/birth defect.
- Is judged by the investigator to be a serious or protocol-defined important medical event requiring intervention.

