## **II. Research Content and Technical Key Points**

### **2.1 Research Objectives:**

This study aims to evaluate the potential benefits of adjuvant chemoradiotherapy with or without a simultaneous integrated boost in patients with early-stage cervical cancer who have undergone radical surgery and have full-thickness or outer full-thickness stromal invasion.

- **Primary Objective:** 3-year progression-free survival.
- **Secondary Objectives:** 3-year overall survival rate, acute and late toxicities, and progression patterns.

Progression-free survival (PFS): PFS is defined as time from randomization to first radiological/histopathological progression or all-cause death.

Overall survival (OS): Refers to the time period from the date of receiving study treatment to the date of death (any cause). Subjects without an observed death will be censored at the time of confirmed survival.

Acute and late toxicities: KPS score, vital signs, Physical examination, laboratory tests (blood routine examination, routine urine and stool test), comprehensive metabolic panel, coagulation test and so on), ECG, Cardiac ultrasound, adverse events (AEs), AEs is recorded based on CTCAE 5.0 criteria.

Progression patterns: Analyze the progression pathways of the disease, including local-regional recurrence (pelvic region/vaginal cuff/para-aortic nodes), distant metastasis (inguinal nodes, intra-abdominal sites, lungs, liver, bones), tumor bed boost local control (absence of recurrence within the contoured SIB volume)

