#### 2.5.7.8 Adverse Event Analysis

The incidence and types of adverse events (AEs) will be summarized for each treatment group.

The severity and relatedness of AEs to the study intervention will also be evaluated and reported.

Comparative analyses of safety data between groups will be performed using appropriate statistical methods (chi - square tests for categorical AE data).

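### The adverse event definition in 2.5.5 stops with treatment, so it does not cover the late toxicity that 2.1 makes a secondary endpoint, and two CTCAE versions are named

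*Protocol*

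**What the plan says.** Protocol 2.1 lists the secondary objectives as "3-year overall survival rate, acute and late toxicities, and progression patterns". It describes how toxicity is assessed: performance status, vital signs, examination, laboratory tests, cardiac tests and AEs. For grading it states that "AEs is recorded based on CTCAE 5.0 criteria".

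Protocol 2.5.5 opens with the definition of an AE: "any unfavorable medical event occurring in a patient or clinical study subject during the course of radiotherapy and chemotherapy". A later sentence in the same paragraph describes AEs as signs, or any "symptom, or disease temporally associated with the study drug administration". The list below it ends with "Any unfavorable event occurring during the reporting period specified in the protocol that the investigator considers related to the drug or device".

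Protocol 2.5.2 says that all toxicities are graded by the "Common Terminology Criteria for Adverse Events (CTCAE) version 4.0".

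Protocol 2.5.7.8 summarizes and compares AEs by treatment group and mentions "chi - square tests for categorical AE data" as the method. It has no separate item for late toxicity.

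**The concern.** The endpoint and the definition that feeds it do not fit together. Late toxicity is by nature something seen after treatment, and the definition closes when treatment ends. The sentence on study drug makes the fit worse: both groups receive cisplatin, and what separates them is the radiation boost. Staff who follow 2.5.5 to the letter would have no instruction to record a non-serious bowel, bladder or vaginal problem that first appears a year after radiotherapy. Others, guided by 2.1, might record it.

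The protocol gives reason to want these data. Under 2.5.1.4 the boost volume takes in the posterior bladder wall and extends back to the rectal mesentery. Section 2.5.1.3 sets dose limits for rectum and bladder, and the background calls for care about normal-tissue tolerance at high external beam dose. What counts as an AE and how long it is collected is protocol content, because an analysis plan cannot recover events that no one wrote down.

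The two CTCAE versions are a smaller matter of the same kind: one section sets the grading for the endpoint, another sets it for all toxicities, and they differ.

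**Working it through.** No figure in the plan has to be reproduced to decide this point. It rests on comparing the sections, with one calculation to show how long the AE window is.

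**1. Endpoint against definition**

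| Item | Protocol section | Content |
|---|---|---|
| Endpoint | 2.1 | Acute and late toxicity, assessed partly through AEs |
| AE window | 2.5.5, first sentence | The radiotherapy and chemotherapy course |
| Second link | 2.5.5, same paragraph | Timing relative to study drug |
| Reporting period | 2.5.5, last AE bullet | Said to be given in the protocol; none is given |
| Acute/late boundary | None | Not stated |
| Visits after treatment | 2.5.4 | Scheduled under efficacy; no toxicity grading assigned to them |
| Comparison | 2.5.7.8 | AEs by group |

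The chain runs from 2.1 through 2.5.5 to 2.5.7.8. Because 2.5.7.8 works on AEs, it takes over whatever limit 2.5.5 sets.

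**2. Does other text in 2.5.5 repair the window?**
- One bullet covers suspected reactions to a drug or device and has no date limit of its own. It stands in a list under the time-limited definition, so it does not clearly extend it.
- The definition of a serious adverse event has no time window. A late injury that leads to hospital admission would qualify. A non-serious one would not.
- The reporting period would settle the matter if it were stated.

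**3. Length of the window**
- Inputs: 50.4 Gy in total, from 2.5.1.3, which also states "Conventional fractionation is used, with 1.8 Gy per fraction, 5 fractions per week".
- 50.4 / 1.8 = 28 fractions, which agrees with the 28 fractions of the boost in 2.5.1.4.
- 28 / 5 = 5.6 weeks (2.5.1.3 gives the duration as 5 weeks). Cisplatin is given within this time.
- Against the 3-year follow-up in 2.5.6: 5.6 / (3 × 52) = 3.6%.
- Against 5 years in 2.5.4 (2 years quarterly, then 3 years six-monthly): 5.6 / (5 × 52) = 2.2%.

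These are shares of calendar time only. Section 2.5.4 also mentions examinations during adjuvant chemotherapy, which the protocol does not otherwise describe. If such treatment were given, the window would be longer by an unstated amount, but it would still close with treatment.

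**4. Visits available for late toxicity**
- 2 years × 4 + 3 years × 2 = 8 + 6 = 14 visits.
- Another sentence in 2.5.4 puts the six-monthly phase at 5 years, which would give 8 + 10 = 18.
- On either reading the visits already exist.

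**5. CTCAE version**
- Section 2.1 uses 5.0 for AEs. Section 2.5.2 uses 4.0 and applies it to all toxicities, so it cannot be read as confined to cisplatin adjustment.

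**The case against.** The strongest reply is that the protocol plainly intends to collect late toxicity. Section 2.1 names it. The other assessments listed there carry no time limit. Section 2.5.4 keeps patients under review for years whether or not they complete treatment, and serious events have no window. This stands as far as it goes. A reader might infer that the trial would collect acute toxicity only, and the documents do not support that. They support a contradiction under which non-serious late events may be missed or handled unevenly.

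Three further inferences also go too far.
- **The time shares as a measure of loss.** That over 95% of follow-up falls outside the window says nothing about how many events occur there.
- **Late toxicity as the main expected harm of the boost.** The protocol shows which organs lie near the boost and asks for caution, but it does not rank the harms.
- **The chi-square test as an error.** Section 2.5.7.8 names it for categorical data within a broader reference to suitable methods. Section 2.5.7.5.2 provides Kaplan-Meier, log-rank and Cox methods for time-to-event outcomes and extends similar methods to secondary outcomes. The detail may properly sit in the SAP, which is not at hand.

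On CTCAE, the reply is that several dose rules use absolute laboratory values and do not depend on the version. That is true of some rules, while others use grades. The documents do not show any grade that would change between versions, so the conflict is real but its effect is not shown.

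**Conclusion.** The point holds. A stated definition in 2.5.5 does not cover part of a stated secondary endpoint in 2.1, and nothing else in the protocol clearly repairs it. The consequence is that non-serious toxicity after treatment could go unrecorded or be recorded inconsistently, so the safety comparison between arms may not cover late toxicity. The size cannot be given as a number of events, because the documents give no late-toxicity rates. The primary analysis is not affected.

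The conclusion assumes that 2.5.5 is applied as written and that no case report form instruction outside the protocol sets a longer period. If one does, the protocol still has to be brought into line with it.

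The two CTCAE versions are a confirmed inconsistency that needs reconciling, with no demonstrated effect on any result.

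**What to change.** - Amend 2.5.5 so that AEs are recorded from randomization through treatment, and so that late radiotherapy toxicities are graded at each follow-up visit in 2.5.4 to the end of follow-up.
- State the time boundary between acute and late toxicity, and state the reporting period that 2.5.5 refers to.
- Word the definition so that it covers the radiation boost as well as study drug.
- Make clear in 2.5.7.8 that late toxicity is part of the comparison. Time-to-event reporting of late toxicity is optional and can be set in the SAP.
- Reconcile 2.1 and 2.5.2 to one CTCAE version.

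The cost is protocol wording and one late-toxicity page in the case report form, completed at visits that are already planned. The change should be made early, because late events not recorded at the time may not be recoverable afterwards.
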